### 2.3. Interventions

Based on the methodology used by Javaloyes et al. [24] and Vesterinen et al. [31], the intervention will be divided into two training periods for both study groups (HRV-G and TRAD-G): a four-week preparation period (PR) and an eight-week training period (TR). Both will maintain the weekly training volume. The training carried out will mainly be running. The PR period will be common to both groups and will be a familiarization phase for the training sessions and their intensities. During this period, the training intensity will gradually increase for the first three weeks and then decrease in the fourth week. This will mean three weeks of overloading and one week of recovery (3:1). The training to be carried out by the athletes is presented in more detail in Table 1. In the TR period, each group will carry out the corresponding intervention. The TRAD-G group will train according to a predefined training program, which will include sessions carried out at low intensity (approximately 50% of the total), and other sessions of moderate and high intensity, with a structure similar to that carried out during the PR period (Table 2). The training prescribed to the HRV-G group will depend on the subjects’ HRV, in accordance with authors such as Javaloyes et al. [24], Kiviniemi, Hautala, Kinnunen, and Tulppo [34], and Lamberts, Swart, Noakes, and Lambert [35].

To quantify the HRV, a Smartphone application known as “HRV4Training” (see http://www.hrv4training.com/) will be used. This tool has been validated by Plews et al. [36], showing a low typical estimate error (CV% (90% CI) = 3.8 (3.1; 5.0)) and a clear electrocardiographical correlation (r = 1.00 (1.00; 1.00)). It provides the root mean sum of the successive differences between R – R intervals (rMSSD) data using photoplethysmography. rMSSD is more suitable and reliable than other indexes [13,37]; nonetheless, the HRV data will be transformed by taking the natural logarithm, thus allowing parametric statistical comparisons that assume a normal distribution. In this way, a 7-day rolling average will be calculated (LnrMSSD_7-d_). The PR period will be used as a standardized phase to obtain the baseline LnrMSSD_7-d_ and its range of normality (upper and lower limits). Following the indications of Plews, Laursen, Kilding, and Buchheit [38], this will be calculated as the mean ± 0.5 × SD. During the TR period, the LnrMSSD_7-d_ will be calculated daily in order to adapt the training prescribed to the HRV-G athletes. Moreover, the range of normality will be updated weekly. If the LnrMSSD_7-d_ is within the range of normality, the athletes will perform a moderate or high-intensity session. If the weekly LnrMSSD_7-d_ average falls below the normal range, a low intensity workout or rest will be undertaken. Athletes will perform a maximum of two consecutive sessions of moderate or high intensity; likewise, they will not accumulate more than two consecutive rest sessions. The modified scheme of Kiviniemi et al. [34] presented in Figure 1 will be followed.

In accordance with Javaloyes et al. [24], all participants will be instructed to measure their HRV data at home each morning after waking up and emptying their bladders. They will be instructed to lie in a supine position and not perform any further activity during the recordings. Data will be recorded over a 60-s period e.g., [36]. The daily control and recording of the rMSSD, as well as the LnrMSSD_7-d_ calculation used to prescribe the training of the HRV-G athletes, will always be carried out by the trial steering members. These members will receive the information from each athlete via phone or email and, in turn, will inform the HRV-G coach of the training intensity corresponding to each athlete. This procedure will also serve as a strategy for maintaining and monitoring the athletes’ adherence to the training programs. Concomitant care, or any other intervention, will not be allowed during the trial for either the HRV-G or the TRAD-G. Athletes from both groups will carry out the training in their usual location.

### 2.4. Outcomes

The primary outcome of this study will be the maximal oxygen uptake (VO_2max_) obtained in an incremental treadmill test. The secondary outcomes will be: the maximal speed in m/s, maximal heart rate, respiratory exchange ratio, ventilatory thresholds (VT1 and VT2) and their derived speed, heart rate, respiratory exchange ratio and VO_2_ obtained in the incremental treadmill test. Other measurements considered as secondary outcomes will be: the time, speed, heart rate, rating of perceived exertion (RPE) and lactate in the 3000 m running test. Body composition and rMSSD will be considered as other variables.

Measurements will be taken before and after the training period, which will correspond to weeks 5 (pretest) and 12 (post-test). Over the assessment weeks, care will be taken that participants do not carry out any high-intensity training sessions. Each assessment week will consist of two testing sessions with a 48-h recovery period. The first testing session will include maximal graded exercise test and body composition measurements. In the second testing session, athletes will perform a 3000 m running test. The rMSSD will be measured daily, as explained in the intervention section.

The incremental treadmill test will be performed by the Physical Exercise and Human Performance Research Group at the University of Murcia (Spain). This is a more objective way of determining physical fitness and represents the maximal performance capacity of an individual [39]. First, with the athlete in the supine position, a cardiovascular examination will be carried out at rest by means of cardiac auscultation, blood pressure and an electrocardiogram (ECG). The electrodes for recording the ECG and heart rate will be kept in place throughout the test. The Cardioline Cube^®^ electrocardiograph will be used. To perform the incremental treadmill test, the Runner srl (Cavezzo Italy) treadmill will be used, as it was in other studies such as Ballesta-García, Martínez-González-Moro, Ramos-Campo, and Carrasco-Poyatos [40]. Similar to other studies, such as Nuuttila et al. [30] or Vesterinen et al. [31], a prior 2-min aerobic warm up will be performed at 6 km/h. The test itself will start at a velocity of 7 km/h. The speed will be increased by 0.1 km/h every 6 s. The incline will remain at 1% throughout the test. The athletes will be encouraged to perform at maximum effort. The test will end when the subject can no longer run; the subject will indicate this with a hand gesture. The recovery phase will then begin at 4km/h for 3 min followed by rest for a further 2 min. The tests will be considered maximal and valid when the theoretical heart rate (220-age) exceeds 85% and the respiratory exchange ratio (RER) is greater than 1.15 [41]. During the stress test, the subjects will breathe through a mask connected to a gas analyzer (Metalyzer 3b^®^, Cortex, Leipzig, Germany). All gas exchange parameters will be measured breath-by-breath and averaged every 30 s. The VO_2max_ will be defined as the oxygen consumption plateau [42]. The aerobic (VT1) and anaerobic (VT2) thresholds will be determined. Before each test, the gas analyzer will be manually calibrated. The test’s maximal speed (V_max_), maximal heart rate (HR_max_), and respiratory exchange ratio (RER) will be recorded. The V_max_ or HR_max_ will be defined as the highest speed, or heart rate, reached for a finished stage. The speed, heart rate, respiratory exchange ratio and VO_2_ at each ventilatory threshold will also be recorded as V_VT1,_ V_VT2_, HR_VT1_, HR_VT2_, RER_VT1_, RER_VT2_, VO_2VT1_, and VO_2VT2_, respectively. All tests will be carried out under similar environmental conditions (an ambient temperature of 20–22 degrees).

As in other studies [30,43], the 3000 m running test will be conducted individually on a 400 m outdoor running track. Participants will be instructed to run at their maximum speed. Before the test, a 15 min standardized aerobic warm-up will be performed, consisting of running at a low to moderate intensity. Capillary blood samples (5 μL) for blood lactate concentration analysis will be taken from the fingertip using a Scout+ analyzer (SensLab GmbH, Leipzig, Germany). Lactate is considered a useful indicator for measuring the metabolic cost and intensity of effort in aerobic-anaerobic sports [44]. Following Ribas [45], it will be considered in this test to relate it to running intensity. Lactate samples will be taken at four different points in time, in accordance with Rodríguez and Valero [46]: (i) just before the test (Lactate_pre_), (ii) just after the test (Lactate_post_), (iii) 3 min after the test (Lactate_post3_) and iv) 5 min after the test (Lactate_post5_). Other variables, such as heart rate, time, speed, and rated perceived exertion (RPE), will also be measured. Heart rate will be recorded at five different points in time: (i) just before the test (HR_pre_), (ii) just after the test (HR_post_), (iii) 1 min after the test (HR_post1_), (iv) 3 min after the test (HR_post3_) and v) 5 min after the test (HR_post5_). The time will be recorded every 1000 m at three different points in time: (i) after running 1000 m, (ii) after running 2000 m and (iii) after running 3000 m (right at the end of the test). The speed will be calculated from these three points using the formula: speed = distance in m/time in seconds. The RPE will be measured at the end of the test using the modified Börg CR-10 scale of perceived exertion [47]. According to the authors, a 0 rating corresponds to rest; a 3 rating to moderate intensity; a 5 rating to hard intensity; a 7 rating to very hard intensity; and a 10 rating to maximal intensity. This tool has recently been determined as a stand-alone method for training load monitoring purposes in several sports and physical activities with men and women in different age categories (children, adolescents and adults) at various expertise levels [48].

Body composition will be analyzed just before the treadmill test using the InBody120 analyzer (Biospace Co. Ltd., Seoul, South Korea). Height will be measured using a measuring rod (Seca 213), and the body mass index (BMI) will be calculated according to the formula: BMI = kg/m^2^.

The time schedule for enrolment, interventions and assessments is shown in Figure 2.

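### Week 5 both bars and schedules a high-intensity session for TRAD-G, and training load before the week-12 post-tests is fixed as low for TRAD-G but not for HRV-G

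*Protocol article*

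**What the plan says.** Section 2.3 divides the 12 weeks into "a four-week preparation period (PR) and an eight-week training period (TR"), so the training period is weeks 5 to 12, as Table 2 also numbers them. The arms part at that point: "In the TR period, each group will carry out the corresponding intervention".

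Section 2.4 sets the test calendar: "Measurements will be taken before and after the training period, which will correspond to weeks 5 (pretest) and 12 (post-test"). For those weeks it adds that "care will be taken that participants do not carry out any high-intensity training sessions". On the layout of testing it says: "Each assessment week will consist of two testing sessions with a 48-h recovery period". The treadmill test comes first and the 3000 m run second.

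Table 2, which is for TRAD-G only, lists one 50-minute session at VT2 in the High Intensity column of week 5. In week 12 its high and moderate cells are empty, leaving 3 to 4 short low-intensity sessions.

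HRV-G has no weekly table for the training period. Its rule in section 2.3 is that, when the 7-day HRV average is "within the range of normality, the athletes will perform a moderate or high-intensity session". Low intensity or rest follows only when the average is below range. A further limit is: "Athletes will perform a maximum of two consecutive sessions of moderate or high intensity". No exception for week 12 is stated.

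**The concern.** There are two separate problems.

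First, the text and the table give opposite instructions for week 5. The bar in section 2.4 covers the assessment week, not only the days before a test, so holding the VT2 session after testing still breaks it as worded. A coach cannot follow both, and the comparator's training dose is unclear by one session. Section 2.2 also excludes athletes who complete less than 90% of workouts, so it matters whether that session counts.

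Second, the primary outcome is VO2max on the treadmill. The preceding training is matched before the pretest if that test opens week 5, because week 4 is low-intensity only and common to both arms (Table 1). It is not matched in the same way before the post-test. In week 12 one arm is scheduled to train lightly, while the other may be doing moderate sessions. A difference in recovery state that goes with the arm does not average out over athletes and would be read as part of the programme effect.

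**Working it through.** The plan states no figure to reproduce on this point. The check compares its calendar with its schedules and counts sessions and days.

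**Calendar.** The preparation period is weeks 1–4 and the training period is weeks 5–12 (section 2.3, Table 2), which is 8 × 7 = 56 days. Week 5 is days 1–7 of the training period and week 12 is days 50–56. The two assessment weeks are therefore its first and last weeks.

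**TRAD-G sessions in Table 2.**

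| Week | 5 | 6 | 7 | 8 | 9 | 10 | 11 | 12 | Total |
|---|---|---|---|---|---|---|---|---|---|
| High | 1 | 1 | 2 | 0 | 1 | 0 | 2 | 0 | 7 |
| Moderate | 0 | 1 | 1 | 0 | 0 | 1 | 1 | 0 | 4 |
| Sum | 1 | 2 | 3 | 0 | 1 | 1 | 3 | 0 | 11 |

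One of the 7 high-intensity sessions is in week 5, where section 2.4 bars them: 1/7 = 14%. Week 12 has none, so the bar and the table agree there.

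**Week 12, the arms side by side.**

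| | TRAD-G | HRV-G |
|---|---|---|
| High | none scheduled; barred | barred (section 2.4 covers all participants) |
| Moderate | none scheduled | prescribed if HRV is in range (section 2.3) |
| Low or rest | 3–4 low sessions | only if HRV is below range |

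The contrast is low-only against up to moderate, not against high.

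**Days exposed before the treadmill post-test.** Put the treadmill test on day *k* of the week and the 3000 m run on day *k* + 2 (48 h). Both fit in one week for *k* = 1 to 5, so *k* − 1 = 0 to 4 days of week 12 precede the treadmill test.

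**Ceiling on moderate sessions.** Assume one session a day, HRV in range throughout and never three harder sessions in a row. Then 0, 1, 2, 3 or 4 days allow HRV-G at most 0, 1, 2, 2 or 3 moderate sessions, against 0 for TRAD-G. This is what the rules permit, not what is expected.

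**Interval between tests.** With the same weekday in weeks 5 and 12 it is 7 × 7 = 49 days. With treadmill tests on day 1 of week 5 and day 5 of week 12 it would be 49 + 4 = 53 days.

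**Check of the proposed layout (days 3 and 5).** In week 5, days 6 and 7 remain free for the TRAD-G VT2 session. In week 12, days 1 and 2 are the low-only days before the treadmill test. Group-specific training then runs from day 6 to day 49 of the training period: 49 − 6 + 1 = 44 days.

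**The case against.** The strongest reply concerns week 12. Figure 2, the schedule of interventions and assessments, is not available here and may give the test days. If the treadmill post-test is on day 1, no week-12 day precedes it. The days before it then belong to week 11, where TRAD-G has two high-intensity sessions and one moderate session. This stands: the imbalance before the primary test depends on the test day and may be nil within week 12. It does not settle the matter, because no common rule on load would then govern the days before that test either.

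It can also be said that adapting load to HRV is the intervention, and that nothing states that HRV-G will do moderate sessions in that week. Both are true. But section 2.4 already overrides the HRV rule for high intensity in test weeks, so the authors accept that load around testing should be controlled. They stopped one level short of what TRAD-G's table does. Section 2.3 also says weekly training volume will be maintained. Whether that refers to the periods or the groups is unclear, and it does not fix intensity.

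A reader might infer three stronger things that the documents do not support:

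- *That group-specific training contaminates the pretest.* The text places the pretest before the training period, so it may well open week 5, and the VT2 session can follow both tests.
- *That a 7-week interval contradicts the 8 weeks stated.* The 8 weeks are the length of the training period. No interval between tests is stated, 49 days assumes equal weekdays, and the interval is the same for both arms.
- *That HRV-G will be more tired at the post-test and VO2max biased against it.* Neither the size nor the direction of an effect can be derived, and an HRV-G athlete below range would also train lightly or rest.

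**Conclusion.** The point holds in two parts of different strength. The week-5 conflict is certain on the printed text and does not depend on Figure 2: 1 of 7 TRAD-G high-intensity sessions falls in a week where the bar applies. The week-12 difference is a gap in the rules rather than a demonstrated bias. TRAD-G is low-only, while HRV-G remains open to moderate sessions. It bears on the treadmill test for 0 to 4 days according to the test day, and on the 3000 m test through any days of week 12 before it. The ceiling of 0 to 3 moderate sessions rests on the assumptions given with it.

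The effect on VO2max is unknown in size and direction, and may be small. The point is still worth correcting, because the remedy is cheap and removes both a conflict in the instructions and a possible arm difference in recovery before the primary outcome.

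**What to change.** Amend sections 2.3 and 2.4 as follows.

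1. State that both pretest sessions are completed early in week 5, before any group-specific session.
2. In week 5, limit the bar on high intensity to the days up to the second test, and hold the TRAD-G VT2 session after it. No session is dropped or moved to another week.
3. From a fixed number of days before the treadmill post-test (for example 2) until the 3000 m post-test is done, allow only low intensity or rest in both arms, overriding the HRV rule. Counting back from the test keeps the rule valid on whichever weekday it falls.
4. Use the same weekdays for pretest and post-test, for example treadmill on day 3 and 3000 m on day 5.
5. Report the actual interval between tests (49 days with equal weekdays).

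Moving the VT2 session to week 10, which has no high-intensity session, is less good. It would change the high-plus-moderate sequence of weeks 5–8 from 1-2-3-0 to 0-2-3-0 and so depart from the pattern of the preparation period that section 2.3 says TRAD-G will follow. Moving the pretest into week 4 would put maximal tests inside the period whose HRV readings set each athlete's normal range ("The PR period will be used as a standardized phase to obtain the baseline"), and would need its own rule for those readings.

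The cost is a short amendment with no extra tests or participants. The downside is that HRV guidance is suspended for a few days in the test weeks. In the example, 44 of the 56 days remain for group-specific training between the last pretest and the start of week 12.

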### 2.8. Data Analysis

Data will be analyzed using Jamovi (Jamovi Project 2018, version 0.9.1.7, Sydney, Australia) and RStudio 3.15.0 software (PBC, Boston, MA, USA). Prior to data analysis, the Shapiro Wilk test and the Levene test will be performed to determine the normal distribution of the variables and the homogeneity of variance. Descriptive data will be reported as mean ± SD and range. All the data will be analyzed based on the intention-to-treat principle (last observation carried forward). If the sample is normally distributed, Student’s t-test will be calculated to compare variables before and after the intervention. For a variable to be considered as having a normal distribution, 95% of values will have to be within two standard deviations of the mean. If the sample is nonparametric, the U-Mann Whitney test will be used to compare variables before and after the intervention. The standardized mean differences (Cohen’s effect size) will be calculated together with the 95% confidence intervals [49]. The effect sizes (ES) will be calculated using Cohen’s d [49]. The relationship between variables will be assessed using the Pearson r correlation coefficient. If r is higher than 0.7, the determination coefficient (r^2^) will be used to determine the percentage of Y variation with regard to the X variation. Significance will be accepted at *p* ≤ 0.05.

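### Within-arm change in the outdoor 3000 m test mixes training with conditions on the two test dates; rest the conclusion on the between-arm difference in change and test the arms together

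*Protocol article*

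**What the plan says.** Section 2.4 (Outcomes) of the protocol article says that "the 3000 m running test will be conducted individually on a 400 m outdoor running track". On timing it says: "Measurements will be taken before and after the training period, which will correspond to weeks 5 (pretest) and 12 (post-test"). The role of the test is secondary: "Other measurements considered as secondary outcomes will be: the time, speed, heart rate, rating of perceived exertion (RPE) and lactate in the 3000 m running".

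The paragraph on the treadmill test ends with "All tests will be carried out under similar environmental conditions (an ambient temperature of 20–22 degrees"). The 3000 m description starts directly after it. For the track test itself the stated standardisation is "Before the test, a 15 min standardized aerobic warm-up will be performed". For the assessment weeks, "Each assessment week will consist of two testing sessions with a 48-h recovery period", and high-intensity training is avoided.

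Section 2.8 (Data Analysis) states that, for normally distributed data, "Student’s t-test will be calculated to compare variables before and after the intervention". Objective (i) in the Introduction is change after either training period, and objective (ii) is the difference between the two protocols. The Discussion expects both arms to improve in 3000 m time, speed, heart rate, perceived exertion and lactate.

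Section 2.1 draws the athletes from two institutions in different towns. Section 2.6 tells coaches what will be required if their club is randomised to HRV-G.

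**The concern.** An outdoor run at maximal effort responds to temperature and wind as well as to fitness. If conditions differ between week 5 and week 12, athletes tested under them tend to move in the same direction, and a before-after test within an arm cannot tell that movement from a training response. Objective (i) and the Discussion read exactly that within-arm change as the effect of training.

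The between-arm contrast is protected only if both arms meet the same conditions. If whole clubs are the randomised units, club and arm coincide. Testing one club on one day and the other on another day, or on another track, would then put any difference in conditions entirely into the arm comparison.

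**Working it through.** The plan gives no figure for a conditions effect, so there is none to reproduce. The check sets the passages side by side and then illustrates the consequence.

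**1. Interval.** Week 12 − week 5 = 7 weeks between the two track tests.

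**2. What the temperature sentence covers.** Within its paragraph, the tests referred to are treadmill tests, so the natural reading is that it applies to the treadmill only. The track test then has no stated environmental condition. On the literal reading it covers the track test too. The plan then promises a band of 22 − 20 = 2 degrees that cannot be set on an outdoor track, and wind is still not addressed. Either way the sentence needs its scope fixed.

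**3. What each comparison estimates.** Write T for the training effect on 3000 m time and C for the shift due to conditions between the two dates.

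- Change in HRV-G = T_HRV + C_HRV
- Change in TRAD-G = T_TRAD + C_TRAD
- Difference in change = (T_HRV − T_TRAD) + (C_HRV − C_TRAD)

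Each within-arm change keeps its own C whatever the scheduling. The difference in change is free of it only when C_HRV = C_TRAD.

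**4. Illustration.** Inputs: n = 7 per arm (Section 2.5); significance at 0.05 (Section 2.8), taken as two-sided because the article does not say; no true training effect; a shift of δ SDs of the athletes' change scores, common to all athletes tested under it. The values of δ are assumptions.

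- Within one arm: paired t-test, 6 df, noncentrality δ√7 = 2.646δ.
- Between arms, with only one arm shifted: two-sample t-test on change, 12 df, noncentrality δ√(7/2) = 1.871δ.

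| Assumed δ | Noncentrality, within | False within-arm change | Noncentrality, between | False arm difference, one arm shifted | False arm difference, shift shared |
|---|---|---|---|---|---|
| 0 | 0 | 5% | 0 | 5% | 5% |
| 0.25 | 0.661 | 9% | 0.468 | 7% | 5% |
| 0.5 | 1.323 | 20% | 0.935 | 14% | 5% |
| 1.0 | 2.646 | 60% | 1.871 | 41% | 5% |
| 1.5 | 3.969 | 91% | 2.806 | 73% | 5% |

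The last column is the point of the remedy: when both arms share the conditions, the between-arm test keeps its 5% level whatever the shift.

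**The case against.** Several replies have force.

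- **Conditions are addressed.** A reader might infer that the track test has no control of conditions at all. The documents do not support that. The temperature sentence is worded to cover every test and can be read to include the track, and a standardised warm-up, the 48-h gap and the avoidance of high-intensity training are stated. What remains is that the temperature cannot be set outdoors and wind is not mentioned.
- **The trial has a concurrent comparator.** A shared shift cancels for objective (ii). This stands, and the fix builds on it.
- **Separate testing of the arms is not stated.** A reader might infer that the arm difference is biased. The article does not say that the clubs are tested on different days or tracks. It mentions a track in the singular and one assessment week at each time point, and the remark in Section 2.3 about usual locations concerns training, not testing. Nor is the unit of allocation uniform: Section 2.6 speaks of clubs, Section 2.7 of participants. Between-arm bias is a risk left open, not an established fault.
- **An article condenses the protocol.** Running order and weather logs may well be in a fuller document, so their absence alone is no finding. The point rests on what is stated: a before-after reading of an outdoor test, and a temperature condition of unclear scope.
- **The problem is common to any before-after comparison.** True, but here an external source of change is built into the test, and the Discussion relies on the within-arm change.

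Two further inferences should be avoided. The 3000 m run is not the only running-performance outcome, since maximal treadmill speed and the speeds at both ventilatory thresholds are also listed. And the 1.1 in Section 2.5 cannot serve as a yardstick for a weather effect: it is called an estimated error in a precision formula, not a target effect, and a percentage of VO2max is not interchangeable with a percentage of running time.

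**Conclusion.** The point holds for the within-arm 3000 m results. As planned, a before-after difference in an arm cannot be attributed to training, because a difference in conditions between the two dates has the same appearance. For the between-arm contrast the documents support only a conditional statement: it is protected if both arms are tested under shared conditions, which the article does not secure, and it would be confounded if clubs are the randomised units and are tested separately.

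The size is unknown. Under the assumed shifts of 0.25 to 1.5 SD of change, false within-arm findings rise from the nominal 5% to between 9% and 91%; if only one arm is affected, false arm differences rise to between 7% and 73%. These rates assume no training effect, a two-sided 5% test and a shift common to all athletes concerned. Only secondary outcomes are touched. The primary outcome, VO2max, is measured on the treadmill at the stated temperature and is unaffected.

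**What to change.** In Section 2.8, state that the conclusion on the 3000 m outcomes rests on the HRV-G minus TRAD-G difference in change, and that change within an arm is descriptive only.

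In the 3000 m description in Section 2.4:

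- use the same track for both arms;
- include athletes of both arms in every test session;
- keep each athlete's time of day the same at pretest and post-test;
- record temperature and wind at each run.

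A single common day for all 14 athletes (2 × 7) should not be required. If the 48-h gap is kept exactly, it would force all 14 treadmill tests onto one day as well. Several days are acceptable, provided that each contains athletes of both arms.

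Limit the 20–22 degree sentence to the treadmill test.

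No test is added. The cost is some travel and scheduling for the two clubs, a short log at each run, and giving up the claim of a within-arm training effect on the 3000 m outcomes.
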